## Abstract

**Background:**

Peritoneal dialysis (PD) is an effective treatment for end-stage renal disease. It allows patients more freedom to perform daily activities compared to haemodialysis. Key to successful PD is the presence of a well-functioning dialysis catheter. Several complications, such as in- and outflow obstruction, peritonitis, exit-site infections, leakage and migration, can lead to catheter removal and loss of peritoneal access. Currently, different surgical techniques are in practice for PD-catheter placement. The type of insertion technique used may greatly influence the occurrence of complications. In the literature, up to 35% catheter failure has been described when using the open technique and only 13% for the laparoscopic technique. However, a well-designed randomized controlled trial is lacking.

**Methods/Design:**

The LOCI-trial is a multi-center randomized controlled, single-blind trial (pilot). The study compares the laparoscopic with the open technique for PD catheter insertion. The primary objective is to determine the optimum placement technique in order to minimize the incidence of catheter malfunction at 6 weeks postoperatively. Secondary objectives are to determine the best approach to optimize catheter function and to study the quality of life at 6 months postoperatively comparing the two operative techniques.

**Discussion:**

This study will generate evidence on any benefits of laparoscopic versus open PD catheter insertion.

**Trial registration:**

Dutch Trial Register NTR2878

## Background

Approximately 15.000 patients in the Netherlands are diagnosed with end-stage renal disease (ESRD) and are dependent on renal replacement therapy (peritoneal dialysis, haemodialysis or transplantation). Almost 6.300 patients are on dialysis. One fifth is on peritoneal dialysis (PD). PD has several advantages over haemodialysis (HD): it allows patients greater freedom to perform daily activities, it requires fewer dietary restriction, and mortality is lower during the first two years of treatment [1]. The costs may also be of great importance. PD costs up to $43K dollars less than HD per person per year, therefore well-functioning PD may have major economic consequences [2,3]. However, we have noticed that PD catheter insertion has a high rate of technical failure using the standard open technique. Case-series report up to 35% catheter failure with the open technique [4-9]. Catheter malfunction is most commonly caused by complications, such as malpositioning of the catheter tip, in- and outflow obstruction, peritonitis, exit-site infections and leakage. These complications often lead to re-operation and even loss of PD as dialysis modality. For a small but significant number of patients this results in severe morbidity and even mortality. For many other surgical procedures, laparoscopy has proven to be superior to the open techniques, by reducing morbidity, length of hospital stay, postoperative pain and improved convalescence [10-13]. An advantage of laparoscopic PD catheter insertion, compared to the conventional open technique, is the ability to insert the catheter under direct vision. Direct visual feedback during placement, leads to better positioning at the end of the operation [14,15].

In current literature, comparative trials reported no significant difference in the risk of catheter removal, replacement or technical failure between both techniques [9,16-19], however there are no well-designed randomized controlled trials comparing laparoscopic PD catheter insertion to the traditional open technique.

## Methods/Design

### Study objectives

Primary Objective: Does the use of the laparoscopic insertion technique lower the incidence of malfunctioning PD catheters at 6 weeks postoperatively?

Secondary Objectives: Does the use of the laparoscopic insertion technique improve catheter longevity and reduce the rate of surgical complications, mortality, leakage, catheter migration, re-admissions, exit-site infections, peritonitis and duration of hospital stay? Does the use of the laparoscopic insertion technique reduce postoperative pain, the use of postoperative pain medication and increase the quality of life? Does the use of the laparoscopic insertion technique lower the incidence of malfunctioning PD catheters at 6 months postoperatively?

### Study design

The LOCI-trial is a multicenter prospective single blinded, randomized controlled trial. The LOCI-trial has a pilot nature, as the study will generate data that should enable us to design a large multi-center randomised controlled trial comparing the laparoscopic PD insertion technique with the open technique.

The design of this protocol is in accordance with the CONSORT guideline [20]. We have stratified per center, PD in the past and previous episodes of peritonitis. The study has started on May 24^th ^2011 and the duration will be approximately 1.5 years. This study compares laparoscopic and open PD catheter insertion. In total 100 patients will be included in the study. Approval of the Medical Ethical Committee Erasmus MC, Rotterdam, The Netherlands, was obtained.

Randomisation will take place after endotracheal intubation, by means of a web-based computer programme with supervision of the study coordinator. This computer programme will generate the randomisation sequence. The patient will be blinded for the operation technique in the postoperative period. The wounds will be covered with a standard pattern of bandages [21]. All patients will fill out questionnaires (the Short-Form 36 (SF-36), EuroQol (EQ-5D) and a Visual Analogue Scale (VAS) for pain) until 6 months postoperatively. (Table 1)

**Table 1 T1:** Time schedule for filling out the questionnaires

Time of evaluation	VAS	EuroQol	SF-36
Preoperative	X	X	X
Postoperative			
Day 0	X		
Day 1	X		
Day 2	X		
Day 3	X	X	
Week 1	X	X	
Week 2	X	X	
Week 4		X	X
Week 6			X
Week 8			X
Week 12		X	X
Week 26		X	X

### Patient selection

All, Dutch speaking, patients with an indication for PD can be included in this trial. Exclusion criteria are: BMI >35 kg/m^2^, age <18 years and patients who are not able to withstand a laparoscopic procedure. Informed consent is mandatory.

Patients will be informed about this study in the outpatient clinic. Patients can contact the research fellow, a surgeon or an independent physician for further information. If patients will not sign the informed consent form, the PD catheter will be inserted via the open technique (considered standard of care in our center).

### Hypothesis

The laparoscopic PD catheter insertion technique will lead to a lower incidence of malfunctioning catheters at 6 weeks postoperatively.

### Study questions

Primary question: Does the use of the laparoscopic insertion technique lower the incidence of malfunctioning PD catheters at 6 weeks postoperatively?

Secondary questions: Does the use of the laparoscopic insertion technique improve catheter longevity and reduce the rate of surgical complications, mortality, leakage, catheter migration, re-admissions, exit-site infections, peritonitis and duration of hospital stay? Does the use of the laparoscopic insertion technique reduce postoperative pain, the use of postoperative pain medication and increase the quality of life? Does the use of the laparoscopic insertion technique lower the incidence of malfunctioning PD catheters at 6 months postoperatively?

### Sample size calculation

At present, we do not have sufficient data to perform a power analysis. Therefore, this pilot study will include two groups of 50 patients. We anticipate that these 100 patients will be sufficient to indicate a difference in technical failure rate at 6 weeks. We do not expect to find significant differences in secondary end points in this relatively small number of patients. In order to be able to include the number of required patients, this study will take place in multiple hospitals. Based on the outcome of this pilot study, we will design a larger multicenter randomized controlled trial, including a large number of patients based on a power calculation.

### Surgical interventions

Laparoscopic technique: pre-operatively, the surgeon or peritoneal dialysis nurse will have marked the exit place of the catheter together with the patient (left or right), well above the belt.

The patient will be operated under general anaesthesia. Antibiotic prophylaxis (Vancomycin 1000 mg IV) will be administered on the ward approximately 1 hour before incision. Chloorhexidine desinfection will routinely be applied. The patient will be covered with sterile drapes. The patient is put in Trendelenburg position. A small subumbilical incision will be made, the fascia will be opened. A 10-12 mm balloon trocar will be inserted and pneumoperitoneum will be created by gas insufflation. Using a 30 degrees optique, the peritoneal cavity will be inspected. Adhesions will be scored and adhaesiolysis will be performed where necessary to place the catheter. A double-cuffed Swan Neck Tenckhoff dialysis catheter will be placed on the abdomen of the patient, to determine the best entry place and exit point. A small incision is made at the entry point. With an 8 mm trocar, a subcutaneous tunnel is created. The trocar is then introduced in the peritoneal cavity. The catheter will now be introduced with a stylet, without twisting the catheter around the stylet. If necessary, an additional 5 mm trocar is inserted to enable securing of the PD catheter in correct position. The catheter tip will be placed in the pouch of Douglas. The stylet will be retracted and the 8 mm trocar will be removed. The distal cuff of the catheter remains just outside the peritoneum. The peritoneal cavity will be desufflated. The inflow and outflow will be tested with at least 500 cc of saline with the patient in neutral position. This should be very easy. Then the balloon trocar will be removed. The sub umbilical fascia will be closed with Vycril-UR6 and the closure of the skin with Monocryl. After 14 days, PD training can be commenced. Conversion to an open procedure will be performed for indications that are common in laparoscopic procedures.

Open technique: The pre-operative measures are the same as in the experimental intervention. A 4-5 cm pararectal incision will be made, the anterior rectus fascia will be opened, the muscles will be split and the dorsal rectus fascia will be opened. The surgeon ensures that the surrounding peritoneum is free of adhesions with his fingers. Preferably, the os pubis is felt. The catheter will now be introduced as described above and the tip will be placed in the pouch of Douglas. Testing of in- and outflow will be as described above. The peritoneum and fascia will be closed with a purse string suture using PDS 3-0. The proximal end of the catheter will be connected to a Redon needle, and a natural exit point is determined, ensuring that the proximal cuff is far enough from the exit point. Further as above. As with the laparoscopic technique, PD training will be started after 14 days.

### Outcome measures

#### Primary outcome

The percentage of functioning CAPD catheters at 6 weeks postoperatively. This is defined by not having an indication for catheter removal or revision for:

• An in- and/or outflow restriction. Outflow restriction is defined as an outflow time longer than 30 minutes, and urokinase treatment has failed.

• Refractory peritonitis, relapse peritonitis or fungal peritonitis, as described in the national guidelines defined by the Dutch Federation of Nephrology.

• Severe abdominal pain (VAS > 8) for 4 weeks.

• Pericanullar or subcutaneous leakage of peritoneal fluid not improving spontaneously within 5 weeks after catheter insertion.

• Tunnel- or exit-site infection not responding to treatment in 2 weeks (refractory infection).

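### The primary endpoint counts a catheter removed or revised for an unlisted insertion-related reason as functioning, and leaves failed placements without a clear score

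*Protocol article*

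**What the plan says.** Under Outcome measures, the protocol article gives the primary outcome as "The percentage of functioning CAPD catheters at 6 weeks postoperatively". The scoring rule follows: "This is defined by not having an indication for catheter removal or revision for" one of five causes. These are:

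- flow restriction, where "Outflow restriction is defined as an outflow time longer than 30 minutes, and urokinase treatment has failed"
- three kinds of peritonitis (fungal, relapsing and refractory), defined by reference to a national guideline
- severe abdominal pain (VAS above 8) lasting 4 weeks
- "leakage of peritoneal fluid not improving spontaneously within 5 weeks after catheter insertion"
- tunnel or exit-site infection that has not responded to 2 weeks of treatment

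Other sections bear on who is scored. Study design places randomisation after endotracheal intubation. Surgical interventions allows conversion from laparoscopic to open, and says of dialysis training: "After 14 days, PD training can be commenced". Secondary outcomes lists mortality, surgical complications, catheter migration, catheter longevity and 6-month function. Treatment of participating PD patients invokes intention to treat but attaches no scoring rule to it. Sample size calculation sets 50 patients per arm and says that the later, larger trial will be designed from this pilot's outcome.

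**The concern.** The objective and hypothesis ask about malfunctioning catheters, and Sample size calculation speaks of technical failure. The endpoint measures something narrower, namely the absence of five indications. A catheter that is out of the patient by week 6 for a sixth reason has none of the five and therefore passes.

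Because randomisation follows intubation, abandoned insertion and operative injury all happen after randomisation, so they belong in the comparison. They are also events that the choice of technique could plausibly influence. If they are more common in one arm, the primary comparison is biased in favour of that arm. If placement fails and no denominator is fixed, whether to count the patient as a success, a failure or an exclusion could be decided after the results are known. Any resulting error in the failure rate would carry into the planning of the larger trial.

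A smaller issue is timing. Two of the five criteria need a fixed duration that may not have run out by day 42.

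**Working it through.** **No planned figure to reproduce.** The protocol gives no power calculation, so the check concerns how the rule scores particular patients and how much each one weighs.

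**Step 1. Apply the rule literally.**

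| Patient | Score under the written rule |
|---|---|
| Catheter removed before week 6 for refractory exit-site infection | Not functioning (listed) |
| Catheter removed or revised before week 6 for bleeding or visceral injury | Functioning (none of the five causes) |
| Malposition causing flow restriction, urokinase failed | Not functioning (listed) |
| Randomised, catheter could not be placed | Functioning on the negative wording, or outside a percentage of catheters; not stated |
| Died before week 6 | Same ambiguity |

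Only the second row is a clear wrong result from the stated rule. The last two rows are unresolved.

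**Step 2. Weight of one patient.** With 50 per arm (Sample size calculation), 1/50 = 2 percentage points.

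**Step 3. Illustration of sensitivity.** The counts are assumed, since the documents give no frequency for unlisted failures. The test is the planned chi-square, taken uncorrected and two-sided: z = (a/50 − b/50) / √(p(1−p) × 2/50), with p = (a+b)/100.

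- 17 v 7: p = 0.24, z = 0.20/√(0.24 × 0.76 × 0.04) = 0.20/0.0854 = 2.34, p-value 0.019.
- 17 v 8 (one unlisted failure added to the second arm): z = 0.18/√(0.25 × 0.75 × 0.04) = 0.18/0.0866 = 2.08, p-value 0.038.
- 17 v 9 (two added): z = 0.16/√(0.26 × 0.74 × 0.04) = 0.16/0.0877 = 1.82, p-value 0.068.
- 19 v 9 (two added to each arm of 17 v 7): z = 0.20/√(0.28 × 0.72 × 0.04) = 0.20/0.0898 = 2.23, p-value 0.026.

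Two reclassified patients in one arm can therefore move a result across 0.05. The same number in both arms leaves the difference at 20 points. The last line read against the third shows the opposite direction: an observed 17 v 9 becomes 19 v 9 if both unlisted failures were in the first arm.

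**Step 4. Durations against day 42.**

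- Pain: 42 − 28 = 14, so pain starting after day 14 cannot complete 4 weeks. Training may begin from day 14, so pain first appearing once training is under way is affected.
- Infection: 42 − 14 = 28, so an infection first treated after day 28 cannot complete 2 weeks. That is 14 of the 42 days, one third. The whole 42 days is the right base because the criterion is not tied to dialysis use.
- Leakage: judged at a fixed 5 × 7 = day 35 from insertion, whatever the onset. A leak starting on day 34 has one day to improve, which pushes it towards failure. One starting after day 35 is not clearly covered.
- Flow restriction and peritonitis: no duration is stated in this text.

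**The case against.** The strongest reply is that the gap is narrower than it looks. Several parts of that reply stand.

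- **Deaths and failed placements.** A reader might infer that these are all scored as successes. The text does not establish that. A percentage of functioning catheters can equally be read as leaving out patients who have no catheter. They are unclassified, and their handling may be set out in a fuller document that is not shown.
- **Malposition.** The Background says "Catheter malfunction is most commonly caused by complications, such as malpositioning of the catheter tip", so a reader might infer that the main failure mode is missed. It is mostly captured, because its functional result, flow restriction, is the first listed cause. Migration is also reported as a secondary outcome.
- **Late-onset complications.** A reader might infer that these generally become successes. Only the pain and infection criteria behave that way; a late leak tends towards failure. Any fixed-time endpoint also has a boundary, and a patient part-way through treatment has not yet met the stated criterion. Later failures can appear in 6-month function and catheter longevity.
- **Size.** The rates of 35% and 13% in the Abstract are literature figures, the former an upper value. Neither is tied to this definition or used in the design, so no bias in this trial can be computed from them.
- **Pilot status.** The trial is intended to inform a larger one and recruitment has started, so the endpoint should not be changed more than necessary.

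None of this answers the closed list. Removal or revision for an unlisted insertion-related reason is scored as functioning by wording that the article itself fixes, and listing surgical complications as a secondary outcome does not alter that score.

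**Conclusion.** The point holds in limited form. The written rule gives a wrong score to catheters removed or revised by 6 weeks for an unlisted catheter- or insertion-related reason, and it gives no definite score to failed placements or deaths. Each such patient is worth 2 points in an arm of 50. How many there will be, and in which arm, cannot be derived from the documents, so neither the size nor the direction of bias is known. The p-values above show only that two patients could matter, on assumed counts.

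The timing issue is secondary. It affects pain starting after day 14 and infection first treated after day 28. It calls for transparent reporting and a sensitivity analysis, and does not show that the clinical durations are wrong.

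**What to change.** Amend the primary outcome wording before analysis as follows.

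1. **Population:** all randomised patients.
2. **Functioning:** catheter in situ at 6 weeks, with no removal or revision, and no indication for either, for any catheter- or insertion-related reason.
3. **Not functioning:** failed placement, and any removal or revision for such a reason.
4. **Death before 6 weeks:** state one rule in advance, with a sensitivity analysis under the alternative. Counting every death as a failure would attribute unrelated deaths to technique, so the choice should be explicit.
5. **Supportive analysis:** keep the five-indication version.
6. **Criteria still running at day 42:** report the number of patients by arm, and add a sensitivity analysis that classifies them from the existing 6-month follow-up with the clinical durations unchanged. Scheduled VAS scores in Table 1 end at week 2, so for pain this will depend on the patient records.

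The cost is a small change to the endpoint wording after recruitment began. No new visits are needed, and patients already enrolled can be re-scored from the operative and follow-up case record forms and the patient records.

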### Treatment of participating PD patients

All patients will be treated according to the intention to treat principle. Treatment and outpatient clinic visits will be in accordance with the current standard protocol. Patients will be asked to fill out different standardised questionnaires to evaluate pain and nausea (VAS-score), and quality of life (SF-36 and EQ-5D). (Table 1)

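### One component of the 6-week primary endpoint needs VAS above 8 for 4 weeks, but the last scheduled VAS is at week 2

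*Protocol article*

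**What the plan says.** The protocol article, under Primary outcome, sets the endpoint as "The percentage of functioning CAPD catheters at 6 weeks postoperatively". Function is then specified: "This is defined by not having an indication for catheter removal or revision for" any of five listed grounds. The third ground is "Severe abdominal pain (VAS > 8) for 4 weeks".

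Under Study design, Table 1 ("Time schedule for filling out the questionnaires") marks the VAS preoperatively, on days 0, 1, 2 and 3, and at weeks 1 and 2. The later rows carry marks only for the other instruments: EuroQol and SF-36 at week 4, SF-36 at weeks 6 and 8, and both at weeks 12 and 26.

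The sentence that introduces the table lists the SF-36, the EQ-5D "and a Visual Analogue Scale (VAS) for pain) until 6 months postoperatively".

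Two other sections bear on where pain data could come from. Treatment of participating PD patients refers the pain questionnaires back to Table 1 and says of visits: "Treatment and outpatient clinic visits will be in accordance with the current standard protocol". Data collection and access to personal data says that the study coordinator enters follow-up data in the online case record form, but does not list its fields.

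**The concern.** The pain ground is written as a number on a named scale, sustained for a stated time. The article also prints a full schedule for that scale, and the schedule stops well before the stated time can have elapsed. A site that follows Table 1 exactly will not hold the readings that the definition calls for.

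What is at stake is how this component gets decided. Pain is arguably the most subjective of the five grounds. The patient is the one person described as blinded, so the patient's own VAS is the measure best protected against knowledge of the technique. After week 2 that measure is no longer scheduled. A judgement about persistent severe pain would then rest on information gathered by staff who are not described as blinded. The study coordinator, for example, both supervises randomisation and collects the follow-up data.

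**Working it through.** The article gives no figure to reproduce here, so the check compares the time the criterion needs with the time the schedule covers.

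**Inputs**
- Required duration (Primary outcome): 4 weeks = 4 × 7 = 28 days.
- Endpoint (Primary outcome): 6 weeks = 6 × 7 = day 42.
- First and last postoperative VAS (Table 1): day 0 and week 2 = day 14.
- Planned group size (Sample size calculation): 50 per arm.

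**Step 1: longest run the schedule can show.** 14 − 0 = 14 days, and 14/28 is half of what is required. A patient who scores above 8 at every scheduled postoperative reading still shows only two weeks.

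**Step 2: does the start of the pain matter?** A run starting on day s is complete by the endpoint only if s + 28 ≤ 42, so s ≤ 14. The part of that run lying within the VAS schedule is 14 − s days:

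| Start of pain | Run needed | Days within the VAS schedule |
|---|---|---|
| Day 0 | 0 to 28 | 14 |
| Day 7 | 7 to 35 | 7 |
| Day 14 | 14 to 42 | 0 (a single reading) |

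For every possible start the schedule covers at most half of the run. The last 42 − 14 = 28 days before the endpoint contain no scheduled VAS.

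**Step 3: can another scheduled instrument stand in?** The week 4 and week 6 rows hold EuroQol and SF-36, and SF-36 alone. Neither is the VAS score named in the definition. No other section schedules a VAS.

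**Step 4: text against table.** The introductory sentence, taken at its word, puts the VAS on a 6-month course. Table 1, which it cites, ends the VAS at week 2. The sentence therefore cannot be relied on to fill the gap.

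**Step 5: weight of one error.** 1/50 = 2 percentage points in one arm's rate. The number of such errors cannot be estimated, because the article gives no expected frequency for the pain component.

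**Step 6: what two more readings would do.** With the VAS also at days 28 and 42, pain from day 0 is followed to day 28 (28 days), and pain from day 14 is followed through day 28 to day 42 (28 days). Pain from day 7 is seen over days 7 to 28 (21 days) or, if it lasts, days 7 to 42 (35 days). The added readings therefore reach the required span, but a rule is needed for how spaced readings count as 4 weeks.

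**The case against.** The best defence is that the endpoint is a clinical indication for removal or revision, and not a questionnaire score. The other four grounds (flow restriction, peritonitis, leakage, refractory infection) do not appear in Table 1 either. They must reach the database through clinic visits and the case record form, which is checked against patient records at six months. Pain could travel the same way, and a condensed article need not print the form's fields. The VAS in Table 1 also serves a separate secondary outcome, the pain score.

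Much of this stands, and it rules out several stronger readings that a reader might infer:
- **That the component can never be met, or cannot be determined from any trial data.** Clinic or form data might capture it. The article does not say that they do, and does not say that they do not.
- **That the result will be biased towards one technique.** Nothing in the documents gives a direction or a size.
- **That the gap matters only once dialysis training starts after 14 days.** The definition does not tie the pain to catheter use. The argument needs only 14 days against 28.
- **That text and table flatly contradict each other.** The sentence can be read loosely as saying that the set of questionnaires runs to 6 months, with Table 1 giving each instrument's timing. EuroQol and SF-36 do reach week 26. For the VAS, however, sentence and table do not match as written.

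It is also fair to note that this is a self-declared pilot, and that the Background's list of common causes of malfunction does not include pain.

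The defence does not remove the mismatch. This ground is defined by a VAS threshold and a duration, the article prints the VAS schedule, and the two do not fit. If another source is meant, it is not named.

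**Conclusion.** The point holds for the scheduled VAS data. These cover at most 14 postoperative days against 28, so the pain component of the primary endpoint cannot be established from them. It would have to rest on information whose VAS content is unstated. The sentence on 6-month follow-up does not match Table 1 for the VAS.

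This should be corrected, but it does not undermine the primary endpoint as a whole. It touches one of five components, and its effect on the result cannot be computed. The only firm figure is the weight of a single misclassified patient, 2 percentage points in one arm.

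The conclusion assumes that Table 1 is the complete VAS schedule, that the criterion means pain sustained over 28 days after surgery, and that 50 patients per arm are analysed.

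**What to change.** - Add the VAS at weeks 4 and 6. Both time points already carry a questionnaire.
- State that the pain component is scored from these readings, and give the rule by which spaced readings count as 4 weeks.
- Reconcile Table 1 with the sentence on 6-month follow-up, so that the duration of the VAS is the same in both.
- For patients enrolled before the change, flag the missing readings and report a sensitivity analysis of the primary endpoint without the pain component.

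The cost is one extra item at two existing time points and a minor amendment. Readings already missed cannot be recovered, which is why the sensitivity analysis is needed.
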